**Figure 3 figure3:**
[figure not shown]
Implementation outline with example implementation steps. AW-Shift: Assisted Weight-Shift.

#### mHealth Report

The mHealth report will provide summary data and visualizations that provide an informative snapshot of the home testing period (a partial example is shown in Figure 4).

**Figure 4 figure4:**
[figure not shown]
Example of a partial mobile health report. AW-Shift: Assisted Weight-Shift.

#### Integration of the mHealth Report Into the Clinical Electronic Environment

On the basis of the focus group findings, the team will perform the following tasks in collaboration with necessary stakeholders. We will adapt the current, remote data capture process and infrastructure to meet the patient and therapist priorities and requirements for use during the clinical visit. A likely solution for communication of the data will involve the mHealth report being autogenerated on the server and provided back to the patient through the mobile app before the telehealth visit. The patient, being the ultimate owner of their data, will then send their report to their therapist through a secure patient website or mobile app that allows direct communication to the care team and patient access to their web-based medical record. With this data flow plan, the report would be available to the therapist for easy viewing during their visit. In addition, the patient will have full awareness of the data that the clinician is viewing.

#### Iterative Process for User-Designed Implementation of the AW-Shift System Into Clinical Care

Through a series of iterative focus groups and further refinement steps, the team, along with the users of the system (patients and therapists), will co-design the full implementation plan that will be ready for testing in aim 2. We estimate this step will take 2 to 3 iterations of focus groups and refinement steps.

### Specific Aim-2 Methods: Rapid Cycle Quality Improvement

#### Overview

Rapid quality improvement assessment of the implementation plan will be completed in aim 2 by testing the plan with an estimated 10 patients with SCI/D. For the first 3 to 5 patient participants, each participant will be run 1 at a time through the implementation plan. Rapid adjustments will be made as each participant goes through the steps of the plan. For the final 6 to 8 participants, participants will be scheduled in pairs such that at least 2 participants will be run in parallel to test the ability of the implementation plan to adjust to concurrent use of the system in the participants’ home and community. After each participant set, we will make rapid adjustments to optimize the implementation plan. Owing to participant heterogeneity, we will be mindful about how plans will need to be optimized differently depending on patient characteristics such as injury level and whether a caregiver or personal aid is required by the patient to use the system.

#### Protocol for Connected Care Model

Although the specific details of this protocol may change, we propose an outline of the procedures that will occur after participant consent and enrollment.

#### Individualized AW-Shift Prescription

A seating clinic therapist will review the clinical notes of the participant for their seating and mobility history. We presume from our preliminary data from therapists and the knowledge of the clinical team members in this project that a simple initial checklist will be effective in determining the possible “home assignments” that therapists could give to patients to gather the pertinent information specific to the patient, including recording pressure across different surfaces, using weight shift reminders, and recording weight shifts performed during specific tasks. In addition, the patient will be asked to complete a checklist to identify their seating and mobility concerns including, for example, new areas of concern about their skin, seat cushion, weight shifting habits, pressure on other surfaces, sitting posture, or weight relief quantity or quality. On the basis of the checklist information, an individualized prescription will be developed for the participant to fulfill (with extensive team support) during the 2-week daily life testing period.

#### System Setup and Prescription Delivery

The participant will be shipped an AW-Shift system and scheduled for a virtual visit to set up the system by the study coordinator. The system will include the hardware components, a user manual, and a study-provided smartphone or tablet if the participant does not have their own device. If the participant is using their own phone, they will be instructed to download the AW-Shift mobile app from the Apple App Store or Google Play Store. During the system setup visit, the participant will be provided with training regarding how to use the AW-Shift system with the study coordinator and engineering and therapy experts on the study team. The team will review the individualized prescription with the participant, and knowledge about system use will be tested to determine sufficient mastery of using the system.

#### Home and Community Use of the AW-Shift System

Participants will use the system for an estimated 2 weeks before their clinical visit. Participants will have easy access via phone; secure, web-based format; email; and SMS text message for technical and therapy support. A potential prescription could include (but not be limited to) mapping the variety of surfaces the participant sits on in the home and community (the system can be used on any surface), completion of daily weight shift protocols to assess participant positioning on their cushion, measurement of how the participant performs weight shifts with and without reminders provided by AW-Shift, and measurement of the effectiveness of the weight shifts to offload pressure.

#### Summary Report

Before the telehealth clinic visit, the prepared mHealth report will be delivered via the AW-Shift mobile app to the participant. The participant will be instructed about how to upload the report 1 day before their telehealth clinical visit. The therapist will view the mHealth report via the participant’s medical records during the clinical visit.

#### Telehealth Clinical Visit

During the visit, the therapist will use the standard clinical notes and the data provided on the mHealth report to guide the patient participant through the typical steps of a therapy visit focused on the seating and mobility needs related to pressure injury prevention. The telehealth visit will be completed using the standard Zoom interface. The therapist will use all the information they have available to determine the next steps in the patient’s care plan. The clinic visits will be recorded, so that the study team can provide additional observations for use in process improvement. The therapist will ask for confirmation of a skin check performed on the day of the visit with assistance from a caregiver, if necessary.

#### Assessment

Following the telehealth visit, both the patient participants and the therapists will complete a series of surveys to assess usability (System Usability Survey [34]), acceptability (Unified Theory of Acceptance of Use of Technology [35,36]), feasibility (Feasibility of Intervention Measure [37]), and appropriateness [37] of the procedures, and each of them will participate in a short interview to gather qualitative feedback to improve the implementation plan.

#### Rapid Assessment Procedure

Rapid assessment procedures are a pragmatic option for producing timely, contextually rich evaluative information about complex interventions implemented into dynamic clinical settings [38]. We will use rapid assessment procedures after each participant in the first 3 to 5 participants or after each pair of the final 6 to 8 participants to improve the plan for the next set of participants.

#### Stakeholder Input About Case Summaries

The findings from aim 2 will be written as a case summary that will be presented to the patient and therapist focus groups from aim 1 to gather additional stakeholder input about the optimization process. Any points regarding necessary improvement or inconsistencies will be discussed by the research team until consensus is achieved for the final plan for aim 3.

#### Outcome Measures and Data Analysis

The qualitative data from focus groups and interviews will be managed and analyzed as described for aim 1. The quantitative data from the survey scores will be used to define the areas of strengths and weaknesses of the intervention and implementation plan for further refinement.

#### Sample Size

For the rapid assessment testing for aim 2, we provide a robust approach by cycling the process through single and paired visits. Similar to the focus groups, we will sample to attain a breadth of user experiences. A total of 10 participants for each round is an effective sample size to be able to narrow down and optimize the process [33].

#### Data Management

All study data will have unique identifiers removed before the final analysis. Study data will be imported from the various clinical data sets into a central REDCap (Research Electronic Data Capture; Vanderbilt University) database that can be accessed by the study team. The study coordinator managing the database will keep the electronic key secure in accordance with Health Insurance Portability and Accountability Act and patient privacy regulations.

#### Potential Limitations and Alternative Strategies

##### Failure of the System in the Field

We will monitor system use and will be available for troubleshooting. We currently have 25 full systems and will be able to accommodate equipment swapping by mail.

##### Recruitment

We have experienced very little difficulty in reaching our goals for participation in past studies with similar methodology. We will continue to collaborate closely with clinical staff and consumer groups to ensure successful recruitment.

##### Skin Safety

We will continue to track skin safety during the study and will discontinue use if we notice any signs of skin issues.

##### Sensing Technology

The current resistive sensors used in the selected pressure map have inherent limitations including a tendency to creep under prolonged loaded states, but we mitigate this through specific calibration protocols. The mat was selected because it stretches and is durable for whole day use.

### Specific Aim-3 Methods: Pilot

#### Pragmatic Hybrid Implementation Trial

The proposed pilot randomized controlled trial will test whether our novel AW-Shift system intervention adds value to the clinical care of adults with SCI/D to inform our next steps in translation.

#### Study Design

This single-site randomized controlled trial will use a modified intention-to-treat analysis. Randomization will be a stratified, block randomization with stratification based on wheelchair type (manual vs power) and current wound severity (no wound or stage 1 vs stage 2 or stage 3). The intervention group (26/52, 50%) will receive the connected care model that used AW-Shift in combination with telehealth. The control group (26/52, 50%) will receive the standard of care that uses telehealth when appropriate. The statistician will be masked to the group allocation information for the outcome measure analysis.

#### Randomization

We will stratify based on wheelchair type (2 groups: power and manual), and current wound severity (2 groups: no wound or stage 1 and stage 2 or stage 3). We will block randomize in groups of 4. This randomization scheme will ensure distribution of important confounders between arms of the study. Furthermore, the blocking will ensure equal distribution of group assignment during the study.

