#### Study Procedures

For initiation and administration of the intervention, the following procedures will be followed:

Project initiation: The project will be initiated following a study initiation checklist by the PI and local site investigators.Staff training for the intervention: Staff will be instructed about how to use the AW-Shift system, view and use the mHealth report, and administer data collection elements as is appropriate for each study role. Data collection procedures will be standardized and tested for consistency across study team members.Participant recruitment: Recruitment and enrollment during year 2 will occur primarily through clinical staff in collaboration with the study coordinator.Intervention study period: The intervention will begin with 2 weeks of AW-Shift use at home by the patient with SCI/D, followed by a web-based clinical visit with a seating clinic therapist. Before mailing AW-Shift to participants, individualized tasks will be assigned by the seating specialist. The tasks are meant to inform the seating assessment process during the clinical visit. Participants and seating specialists will complete surveys after the seating clinic visit and participate in a guided interview.

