#### Recruitment

Following IRB guidelines, manual and power wheelchair users with traumatic or atraumatic SCI/Ds will be enrolled for the study. The inclusion and exclusion criteria were chosen to include wheelchair users with SCI/D who are at risk for pressure injury development. Recruitment will be purposeful in achieving the desired equal distribution of power and manual wheelchair users and individuals with paraplegia and tetraplegia. For study randomization in aim 3, we will use a stratified, blocked randomization method to ensure even distribution of important predictor and confounding variables in the intervention and control groups. Announcements for participation in this study will be made by personnel directly to patients through mailed letters, phone calls, and word of mouth. Upon determining a person’s eligibility, an appointment (via phone or in person) will be made with the study coordinator to explain the research project, confirm eligibility, and collect the necessary demographic data.

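### A single published block size of 4 in a single-site trial with evident arms lets anyone who knows earlier allocations foresee about 30% of assignments

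*Protocol article*

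**What the plan says.** The aim-3 Study Design section describes one site: "This single-site randomized controlled trial will use a modified intention-to-treat analysis". Allocation is 1:1: "The intervention group (26/52, 50%) will receive the connected care model" and "The control group (26/52, 50%) will receive the standard of care that uses telehealth when appropriate". The same section masks the statistician to allocation for the outcome analysis and names no one else. The raters of the secondary outcome are blinded to identities (Secondary Pilot Clinical Trial Effectiveness Outcomes), which has no bearing on enrolment.

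The Randomization section gives the strata, "We will stratify based on wheelchair type (2 groups: power and manual), and current wound severity", with two levels of each factor and so four cells. It then gives the block size: "We will block randomize in groups of 4". It adds that blocking will *ensure* an equal split between the arms.

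Three sections describe the coordinator's work:
- Study Procedures: "Recruitment and enrollment during year 2 will occur primarily through clinical staff in collaboration with the study coordinator".
- Recruitment (Human Participants): an appointment "will be made with the study coordinator to explain the research project, confirm eligibility".
- System Setup and Prescription Delivery (aim 2): the participant is "scheduled for a virtual visit to set up the system by the study coordinator". The Intervention Protocol section for aim 3 describes its procedure as similar to that of aim 2.

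The section on initiating and conducting the trial adds weekly calls or meetings of all study members.

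**The concern.** In a block of known, constant size the last assignments follow from the earlier ones. Prediction needs two things: the block size, which the article publishes, and the earlier assignments in the stratum. At a single site, where one arm receives a pressure-mapping system and both stratification factors are visible to recruiting staff, the second is easily known.

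Staff who can foresee the next assignment can, without intending to, hasten, delay or discourage a particular patient. Some eligibility criteria call for judgement, such as adequate resources or support for the technology at home. The wound strata are also coarse: no wound is grouped with stage 1, and stage 2 with stage 3. Selection could therefore act within a stratum on features related to healing or recurrence. With 26 patients per arm, covariate adjustment cannot reliably repair selection on unmeasured traits. The results are meant to inform the power of the full trial, so a distortion would carry forward.

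**Working it through.** **Inputs from the article.** Block size 4, ratio 1:1, N = 52, 2 × 2 = 4 strata. **Assumption.** The article gives no stratum sizes; the simulations take the four strata as equally likely.

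**1. The plan's own figure.** 52 / 4 = 13 complete blocks, with 2 per arm in each: 13 × 2 = 26 per arm. The stated 26:26 is reproduced if every block is complete.

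**2. One complete block.** There are 6 equally likely orderings of AABB. An assignment is certain once one arm is used up.

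| Position | P(certain) | P(best guess correct) |
|---|---|---|
| 1 | 0 | 1/2 |
| 2 | 0 | 2/3 |
| 3 | 1/3 | 2/3 |
| 4 | 1 | 1 |

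Certain: (0 + 0 + 1/3 + 1) / 4 = 1/3, or 17.3 of 52. Best guess: (1/2 + 2/3 + 2/3 + 1) / 4 = 17/24 = 70.8%, against 50% by chance.

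**3. Allowing for unfinished blocks.** With exactly 13 patients per stratum, each stratum has three complete blocks and one patient in a fourth. Certain: 4 strata × 3 blocks × 4/3 = 16 of 52 = 30.8%. Best guess: (3 × 17/6 + 1/2) / 13 = 9/13 = 69.2%. Simulation with patients falling at random into four equally likely strata gives 30% certain (15.7 of 52; 95% of trials between 23% and 37%) and a 69% best-guess rate. Stratum probabilities of 0.35/0.35/0.15/0.15 or 0.4/0.4/0.1/0.1 also give 30%.

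**4. Varying the block size.** Same setting, with an observer who knows all past allocations in the stratum and the set of sizes in use, but not the order of sizes:

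| Sizes | Certain | Best guess | Arms differ by 4 or more |
|---|---|---|---|
| 4 only | 30% | 69% | 8% |
| 2, 4 | 10% | 71% | 6% |
| 2, 4, 6 | 3% | 69% | 11% |
| 4, 6 | 6% | 68% | 12% |

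Varying the size removes most of the certain assignments but barely moves the guess rate. Sizes 2 and 4 alone make guessing slightly easier.

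**5. The claim of equal split.** With fixed blocks of 4, unfinished blocks leave the arms exactly 26:26 in about 43% of simulated trials, 2 apart in about 49%, and 4 or more apart in about 8%.

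**The case against.** Four objections have weight.

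- **Roles are partly inferred.** Device set-up by the coordinator is written for aim 2, reaches aim 3 only through a statement of similarity, and comes with a warning that details may change. No section says who holds the list. This stands, and the conclusion is conditional on it. Recruitment and confirmation of eligibility by the coordinator are stated outright.
- **Concealment may be described elsewhere.** A reader might infer that the list is not concealed. The article does not support that: such details are commonly left to the full protocol, and their absence here is no finding. But concealing the list would not remove this problem, which comes from a stated block size and known past assignments.
- **The room for steering is limited.** Wound severity is stratified, active stage-4 wounds at the seating surface are excluded, every participant must be able to use the app, and several prognostic covariates are planned. Steering could act only within a stratum. That narrows the harm without removing it.
- **This is a pilot.** The stakes are lower than in a confirmatory trial, though between-group tests are planned.

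A reader might also infer that the arms could end 30:22. That needs all four strata to stop mid-block with two patients in the same arm, all in the same direction. With equally likely strata the chance is about 1 in 41,000, so it is no practical argument.

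**Conclusion.** The point holds as a weakness in a stated design choice, worth correcting before enrolment. About 30% of allocations, some 16 of 52, could be foreseen with certainty by a person who knows both the block size and every earlier assignment in the stratum. One third applies only if all blocks are complete.

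The figure rests on that knowledge being available, which the single site, the evident device and the coordinator's duties make plausible but do not prove. A reader might go further and conclude that enrolment will be biased. The article shows the opportunity, not the event.

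The statement that blocking ensures equal arms is a minor matter of wording: exact equality is expected in fewer than half of trials, but the difference is usually no more than 2.

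**What to change.** Replace the block-size sentence in the Randomization section with, for example: *Allocation will use computer-generated permuted blocks of randomly varying size within strata; the sizes will not be disclosed to recruiting staff.* Suitable sets are 2, 4 and 6, or 4 and 6. Do not use 2 and 4 alone. Keep the chosen set out of documents that recruiting staff use.

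Because varying the size hardly lowers the guess rate, also arrange, where existing roles allow, that the person confirming eligibility does not track allocations by stratum. Change *ensure* to *promote* in the sentence on equal distribution.

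The cost is a new list and two edited sentences. The article says ethics approval for aims 2 and 3 was still to be sought, so the change could be made before aim-3 enrolment. The statistical price is a somewhat greater chance of unequal arms: a difference of 4 or more in about 11% to 12% of simulated trials instead of about 8%. The theoretical maximum difference rises from 4 × 2 = 8 to 4 × 3 = 12, both remote.

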#### Study Population

Adults with SCI/D with high risk of recurring pressure injury who answer “yes” to one of the following questions are eligible: (1) I get pressure ulcers about every couple of years; (2) I get at least 1 pressure ulcer a year; and (3) I always seem to have sores, often requiring surgery or hospitalization [39]. Our rationale for choosing individuals at high risk for recurring injury is that once a person has one pressure injury, their chances are significantly high to have another; hence, it has been recommended that interventions focus on this group of individuals [39].

#### Initiating and Conducting the Pilot Clinical Trial

The principal investigators (PIs), coinvestigators, and study staff will manage the process of study initiation with a modified standard checklist that covers essential items. Pilot clinical trial initiation meeting will occur early in mid–year 1, wherein all the steps will be reviewed, and the specific timeline will be determined. Standard operating procedures and field guidebooks will be developed to follow throughout the trial period. Weekly phone calls or web-based meetings among all study members will be used for study management. Any urgent communication regarding the pilot clinical trial will be managed with a phone call to the PI made within 18 hours of the event and reported to the IRB.

#### Study Procedures

For initiation and administration of the intervention, the following procedures will be followed:

Project initiation: The project will be initiated following a study initiation checklist by the PI and local site investigators.Staff training for the intervention: Staff will be instructed about how to use the AW-Shift system, view and use the mHealth report, and administer data collection elements as is appropriate for each study role. Data collection procedures will be standardized and tested for consistency across study team members.Participant recruitment: Recruitment and enrollment during year 2 will occur primarily through clinical staff in collaboration with the study coordinator.Intervention study period: The intervention will begin with 2 weeks of AW-Shift use at home by the patient with SCI/D, followed by a web-based clinical visit with a seating clinic therapist. Before mailing AW-Shift to participants, individualized tasks will be assigned by the seating specialist. The tasks are meant to inform the seating assessment process during the clinical visit. Participants and seating specialists will complete surveys after the seating clinic visit and participate in a guided interview.

